#### 3D-pCASL data

For the ASL fMRI data, corresponding CBF images were obtained using an automated image postprocessing tool embedded in the GE healthcare MR-750 system. Subsequently, the CBF images will be spatially normalized to the standard MNI space by using the transformation fields derived from tissue segmentation of structural images and resampled to 3 mm isotropic voxels. The resulting images will be transformed to z scores using Fisher’s transformation approach and then will be smoothed with 8 mm FWHM isotropic Gaussian kernel.

### Statistical analysis

Statistical Package for the Social Sciences (SPSS) 18.0 (SPSS, Chicago, IL, USA) will be used to analyze the socio-demographic and clinical data. SPM8 and REST 1.8 will be used to analyze the imaging data. All statistical tests were conducted with a significance level of 5%.

#### Socio-demographic and clinical data

We will use 2-sample Student-t test for discrete quantitative data (age, body mass index, educational level, migraine history, frequency of migraine attacks, duration of migraine attacks, SAS score, SDS score, MMSE score, MoCA score and MIDAS scores), and the chi-square (χ2) test for nominal qualitative data (gender, type and location of migraine).

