### Subject

All subjects will be provided informed, written consents after the study procedure has been fully explained in detail. Females who match the following criteria would be included in the migraine group: (1) age ranges from 40 to 55 years old; (2) irregular menstrual cycle; (3) suffered from migraine; (4) normal neurological examination. Females who match the following criteria would be included in the HC group: (1) age ranges from 40 to 55 years old; (2) irregular menstrual cycle; (3) not suffered from any kinds of headache; (4) normal neurological examination. Exclusion criteria will be as follows: (1) severe psychiatric disorders, such as dementia, episode, epilepsy, major depression; (2) significant neurological illness, such as significant head trauma, tumor, meningitis or central nervous system (CNS) inflammatory lesions and vascular complications clues; (3) any MRI contraindications; (4) alcohol, nicotine or drug abuse.

Sample size have been estimated by referring to other studies [22, 23]. A sample size of 40 patients per group will be suitable for a power of 0.8 and an alpha significance level of 0.05 (two-side). Considering the drop-out ratio (25%) and unqualified images of included subjects, the total sample size is 55 in each group.

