### Clinical assessments

Demographic and clinical features of all subjects will be collected and recorded, such as age, education level, body mass index (BMI), occupation and menstrual cycle. All participants will receive the following battery of neuropsychological tests: Montreal Cognitive Assessment (MoCA) and Mini-mental State Examination (MMSE) will be used to assess the mental state of subjects. The Short Form health survey (SF-36) will be applied to evaluate the quality of life, and Self-rating Depression Scale (SDS) and Self-rating Anxiety Scale (SAS) will be performed to measure the severity of self-reported depression and anxiety. Migraine will be diagnosed according to the International Headache Society (IHS) criteria of the International Classification of Headache Disorders (ICHD-3 beta version) [1]. The following data will be collected from migraine participants: (1) type of migraine (migraine with aura, migraine without aura, etc.), (2) frequency of migraine attacks, (3) duration of migraine attacks, (4) headache location (unilateral or bilateral), (5) Migraine Disability Assessment Scale (MIDAS) score (the score is divided into 4 grades, higher grade means more severer disability). Blood samples were drawn at the screening centers and processed within 2 h according to a standardized protocol to assess the hormone level [24].

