#### Structural parameters

Both voxel-based and ROI-based 2-sample Student-t test will be applied to compare global gray matter (GMV) MK, MD and FA between susceptible group and healthy control group with age, sex, education and BMI as covariance. Moreover, non-parametric Spearman correlation will be performed to delineate a possible relationship between local morphologic alterations and clinical data as well as diffusional alterations and clinical data. Significance threshold, which is corrected for comparison using Family Wise Error (FWE) method, will be set at *P* < 0.05. For each design matrix, significant effects both in the negative and positive directions are considered.

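### Two-group tests are assigned to variables that are constant or exist only in the migraine group, sex is a redundant covariate, and the grey matter volume models have no head-size term

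*Protocol article*

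**What the plan says.** All references are to the protocol article.

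- *Subject*: both groups are restricted to women ("Females who match the following criteria would be included in the migraine group" and "Females who match the following criteria would be included in the HC group"). Controls must have "not suffered from any kinds of headache". No other groups are defined.
- *Clinical assessments*: migraine type, attack frequency, attack duration, headache location and MIDAS are introduced by "The following data will be collected from migraine participants". The cognitive, mood and quality-of-life scales, by contrast, are for everyone: "All participants will receive the following battery of neuropsychological tests".
- *Socio-demographic and clinical data*: the 2-sample t-test covers age, BMI and education, followed by "migraine history, frequency of migraine attacks, duration of migraine attacks, SAS score, SDS score, MMSE score, MoCA score and MIDAS scores". The chi-square test covers "nominal qualitative data (gender, type and location of migraine").
- *Structural parameters*: GMV, MK, MD and FA are compared between groups "with age, sex, education and BMI as covariance". *Functional and perfusion parameters* repeats the same four covariates for ReHo, ALFF/fALFF and CBF.
- *High-resolution T1WI data*: images are segmented into grey matter, white matter and CSF. The section states neither a modulation setting nor a head-size correction.
- *Primary outcomes measure* names the diffusion parameters. GMV is listed under *Secondary outcomes measure*.

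**The concern.** A two-group test needs a variable that can vary and that is observed in both groups. Gender fails the first condition and the six migraine features fail the second. An analyst who follows the text must either skip these tests or code controls as zero or none, and would then report a P value that only repeats how the groups were formed.

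Sex as a covariate is inert. The risk is one of description: a paper could claim adjustment for sex when the design has already removed sex by restriction.

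Head size is a different kind of issue. The covariate list for GMV is explicit. One of its four terms does nothing, and none stands for head size. If GMV and head size are correlated and the processing does not already remove head size, the comparison loses precision, and a chance imbalance in head size carries over into the GMV difference.

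**Working it through.** **Plan's own figures.** The only related figures are 40 per group, raised to 55. 40/(1 − 0.25) = 53.3, so 54, and 55 fits the added allowance for unusable images. No part of this point depends on that number.

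**1. Which listed variables can be compared.** The t-test list has 11 entries and the chi-square list has 3, so 14 in total.

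- Comparable (7): age, BMI, education, SAS, SDS, MMSE, MoCA.
- Migraine group only (6): attack frequency, attack duration, MIDAS, type and location, all by *Clinical assessments*; and migraine history. Migraine history is not among the items listed there, but it is migraine-only because controls may have no headache.
- Constant (1): gender.

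**2. Gender chi-square.** Degrees of freedom = (groups − 1)(categories − 1) = (2 − 1)(1 − 1) = 0. There is no test.

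**3. Migraine features with controls coded zero.** As an illustration with assumed attack counts (1 plus a Poisson variable of mean 4) in 55 patients against 55 zeros, one simulated data set gave t = 18.7 on 108 df. The result restates the inclusion rule.

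**4. Sex as covariate.** Take the design columns migraine, control, age, sex, education, BMI. With women only, sex = migraine + control, so the six columns have rank 5. The redundant direction is (1, 1, 0, −1, 0, 0). The group contrast (1, −1, 0, 0, 0, 0) is orthogonal to it (1 − 1 = 0), so it remains estimable. Numerical check on simulated data:

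| n per group | Residual df, with / without sex | Group t, with / without sex |
|---|---|---|
| 40 | 75 / 75 | 1.403 / 1.403 |
| 55 | 105 / 105 | 0.927 / 0.927 |

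**5. TIV in the GMV model.** Let r be the GMV-TIV correlation within groups. The article gives no value, so r is an assumption. Residual SD ratio = √(1 − r²). Equivalent sample factor = 1/(1 − r²). With 40 per group, power 0.8 and two-sided alpha 0.05, the detectable difference without TIV is (1.960 + 0.842) × √(2/40) = 0.626 SD. With TIV it is multiplied by the SD ratio (normal approximation, ignoring the one degree of freedom spent).

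| Assumed r | SD ratio | Sample factor | Detectable difference (SD) |
|---|---|---|---|
| 0.5 | 0.87 | 1.3 | 0.54 |
| 0.7 | 0.71 | 2.0 | 0.45 |
| 0.8 | 0.60 | 2.8 | 0.38 |
| 0.9 | 0.44 | 5.3 | 0.27 |

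Without TIV, an assumed chance head-size imbalance of 0.2 SD would shift the GMV difference by 0.2r, which is 0.10 SD at r = 0.5 and 0.18 SD at r = 0.9.

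**The case against.** The list of tests assigns methods by type of data and does not itself say migraine versus control. The entries are descriptive, and no primary or secondary outcome rests on them. *Correlation analysis* already plans regression of imaging on clinical information within migraine patients, so part of the remedy exists. This limits the consequence. It does not rescue the tests, because no migraine subgroups are defined that could supply a second sample.

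On sex, a reader might infer that the imaging results are invalid or wholly unadjusted. The article does not support that. Age, education and BMI still adjust, sex is controlled by restriction, and the group contrast is the same with or without the term. Nor is sex in every imaging model: no covariates are listed for the topological permutation tests, the connectivity measures or the regressions.

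On head size, the objection has most force. A condensed article may leave the modulation setting to the full protocol, and TIV being absent from the covariate list does not show that head size is unhandled in the voxel-wise analysis. The article also gives no reason to expect the groups to differ in head size, so confounding is a possibility and not a finding. What stands is that the list is explicit, that it also governs the global and ROI comparisons, and that no other correction is described.

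**Conclusion.** The contradiction is certain for seven of the 14 listed variables and follows from the text alone: one has no variation and six have no control data. The comparisons of SAS, SDS, MMSE and MoCA are sound. The redundant sex term is equally certain and has no numerical effect.

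The TIV part is a worthwhile improvement to a secondary outcome, conditional on the unstated modulation setting. Its size rests entirely on an assumed r: an equivalent sample 1.3 to 5.3 times as large, for GMV only. A reader might take the upper figure as the trial's loss of efficiency. It is not, since it needs r = 0.9 and does not touch MD, MK or FA.

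A reader might also infer that all seven tests would come out falsely significant. Gender cannot, because a table with 0 degrees of freedom yields no test. The six migraine features would do so only if controls were coded zero.

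Severity: minor. The primary outcome is not affected.

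**What to change.** 1. In *Socio-demographic and clinical data*, delete gender from the chi-square list.
2. In the same section, remove migraine history, attack frequency, attack duration, MIDAS, type and location from the two-group tests. Summarise them in the migraine group and use them in the within-migraine regression already planned under *Correlation analysis*. Keep the comparisons of SAS, SDS, MMSE and MoCA.
3. Delete sex from the covariate lists in *Structural parameters* and *Functional and perfusion parameters*, and state that sex is controlled by enrolling women only.
4. Add TIV (grey matter + white matter + CSF from the planned segmentation) to the global and ROI GMV models. Add it to the voxel-wise model unless the modulation already corrects for head size, and state which applies.

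Cost: small changes of wording and one extra covariate in the GMV models. No new data and no change to the sample size.

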#### Structural parameters

Both voxel-based and ROI-based 2-sample Student-t test will be applied to compare global gray matter (GMV) MK, MD and FA between susceptible group and healthy control group with age, sex, education and BMI as covariance. Moreover, non-parametric Spearman correlation will be performed to delineate a possible relationship between local morphologic alterations and clinical data as well as diffusional alterations and clinical data. Significance threshold, which is corrected for comparison using Family Wise Error (FWE) method, will be set at *P* < 0.05. For each design matrix, significant effects both in the negative and positive directions are considered.

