#### Functional and perfusion parameters

Both voxel-based and ROI-based 2-sample Student-t test will be applied to compare global ReHo, ALFF/fALFF, CBF between susceptible group and healthy control group with age, sex, education and BMI as covariance. The reference time series for headache-related seed regions will be acquired by averaging the time series for all voxels within them. Correlations of this time-series will be calculated to measure FCs among these regions in each participant. To evaluate group differences in the resting-state topological properties, nonparametric permutation tests were applied [29]. Initially, we will calculate the between-group differences of the mean values for each topological property. Next, an empirical distribution of the difference will be obtained by randomly reallocating every property value into two groups and recomputing the mean differences between the two randomized groups (5,000 permutations) to test the null hypothesis that the observed group differences only occurred by chance. The 95th percentile points of each distribution will be used as critical values for a two-tailed test to determine whether the observed group differences could occur by chance. Non-parametric Spearman correlation will also be performed to delineate a possible relationship between functional alterations and clinical data as well as perfusion alterations and clinical data. Significance threshold will be set at *P* < 0.05 (FWE corrected).

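### The imaging–clinical correlations are specified without the age, education and BMI adjustment that the plan applies to the same imaging measures in the group comparisons, so an age or education effect can be reported as a link with migraine

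*Protocol article*

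**What the plan says.** Under Structural parameters, grey matter volume, MK, MD and FA are compared between groups by a two-sample test "with age, sex, education and BMI as covariance". The next sentence says that "non-parametric Spearman correlation will be performed to delineate a possible relationship between local morphologic alterations and clinical data", and extends this to the diffusion measures. No covariate and no partial form is named.

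Under Functional and perfusion parameters, ReHo, ALFF/fALFF and CBF are compared with the same covariate list. Later in that section: "Non-parametric Spearman correlation will also be performed to delineate a possible relationship between functional alterations and clinical data", extended to perfusion, again with no covariates. Both sections set a 5% threshold with family-wise error (FWE) correction.

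Under Correlation analysis, a linear regression among the migraine patients relates imaging properties to cognitive scores and clinical information, also without covariates. The most sensitive parameters then go into an ROC analysis for the degree of migraine and for cognitive decline.

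The clinical variables listed under Socio-demographic and clinical data include "migraine history, frequency of migraine attacks, duration of migraine attacks", as well as MMSE, MoCA and MIDAS scores. Only women are enrolled, so sex is constant and the working covariates are age, education and BMI.

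**The concern.** By adjusting the group comparisons, the plan itself treats age, education and BMI as able to distort these imaging measures. The correlations use the same measures, so that side of the confounding path is the plan's own premise. If a clinical variable also moves with age or education, the two will correlate even when neither bears directly on the other.

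Two kinds of clinical variable are exposed. Years of migraine, if that is what migraine history means, equals current age minus age at onset, so it contains age by construction. MoCA and MMSE scores may vary with education and age (an assumption here).

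The aim of the trial is an imaging measure of severity, and the Discussion says that structural imaging could reflect the long-term impact of migraine. An unadjusted correlation with years of migraine could not be told apart from ageing between 40 and 55. A parameter picked up in this way could be selected for the ROC analysis.

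**Working it through.** **The plan's own figure.** No figure is given for the correlations; the only design figure is the sample size. The article says "A sample size of 40 patients per group will be suitable for a power of 0.8 and an alpha significance level of 0.05 (two-side"), then "Considering the drop-out ratio (25%) and unqualified images of included subjects", "the total sample size is 55 in each group". Check: 40/(1 − 0.25) = 53.3, so 54. The stated 55 agrees, with one woman over for unusable images. The 40 itself cannot be reproduced, because no effect size is given ("Sample size have been estimated by referring to other studies"). The number of migraine patients available for a correlation is therefore about 40, and at most 55.

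**How strongly years of migraine can track age.** Inputs: age 40 to 55 (Subject section), assumed evenly spread; age at onset assumed independent of current age with SD s. The SD of age is 15/√12 = 4.33 years. The correlation of age with (age − onset) is 4.33/√(4.33² + s²):

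| Assumed SD of onset age (years) | Correlation |
|---|---|
| 5 | 0.65 |
| 8 | 0.48 |
| 10 | 0.40 |
| 15 | 0.28 |

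The narrow age range is already included in these values.

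**False-positive rate of the unadjusted correlation.** Let a covariate A correlate a with the imaging measure X and b with the clinical variable Y, with no other link: X = aA + √(1 − a²)e₁ and Y = bA + √(1 − b²)e₂, all normal. X and Y then correlate at a × b, for example 0.5 × 0.5 = 0.25, although there is no direct relation. The partial Spearman is (r_XY − r_XA r_YA)/√((1 − r_XA²)(1 − r_YA²)) on ranks. Simulated rejection at an uncorrected two-sided 5% level, 20,000 samples per row:

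| a / b (assumed) | Unadjusted, n = 40 | Unadjusted, n = 55 |
|---|---|---|
| 0.2 / 0.2 | 5.6% | 5.8% |
| 0.3 / 0.3 | 7.9% | 9.7% |
| 0.4 / 0.4 | 15.9% | 19.8% |
| 0.5 / 0.5 | 31.9% | 41.6% |
| 0.5 / 0.3 | 14.0% | 17.7% |

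Partial Spearman rejects 4.9% to 5.3% in every row. The error grows with sample size, as expected of a bias.

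**Does FWE correction help?** It tightens the threshold but leaves the non-zero correlation in place. At a per-test level of 0.1% and n = 40, the unadjusted test rejects about 0.3% (0.3/0.3), 1% (0.4/0.4) and 3.4% (0.5/0.5), roughly 3, 10 and 34 times nominal. Partial Spearman stays near 0.1%.

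**The case against.** The strongest reply is that the article does not exclude adjustment. It names Spearman correlation, which has a partial form, and covariates for a supporting analysis may be left to an analysis plan that is not shown. This stands only in part. The covariates are listed for one analysis and absent from the next on the same measures, and nothing elsewhere in the article supplies them. An analyst following the text would run the unadjusted test.

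Several further objections stand and limit the point:

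- All the confounder correlations are assumptions. At 0.2/0.2 the inflation is under one percentage point.
- The rejection rates in the main table are at an uncorrected 5%, so they are not the error rates of the planned FWE-corrected procedure.
- Migraine history is not defined. Clinical assessments lists type, attack frequency, attack duration, location and MIDAS, but no years of disease. The age-minus-onset argument reaches none of those listed items.
- The article gives no link between BMI and any clinical variable. BMI is in the proposed set only because it is in the plan's own covariate list.
- Blood hormone level is also clinical data, and the hypothesis concerns estrogen decline. Adjusting that correlation for age could remove part of the signal of interest.

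A reader might infer that age or education effects will be reported as migraine effects. The documents do not support this: it requires the covariate to be related to both the imaging measure and the particular clinical variable, and the article quantifies neither relation. A reader might also infer that the primary result is compromised. It is not. White matter integrity is the primary outcome, its group comparison is adjusted, and the correlations are presented as exploring possible relationships.

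**Conclusion.** The inconsistency is real and lies in what the article fixes: adjusted group comparisons, unadjusted correlations of the same measures, and a regression with no named covariates. The consequence is that age or education effects can be reported as links with migraine for those clinical variables that are themselves related to age or education. The excess ranges from negligible to large: about 5.6% rejection at assumed correlations of 0.2/0.2, and 31–32% at 0.5/0.5, for 40 women at an uncorrected 5% level with no direct link. Which part of the range applies cannot be told from the document. FWE correction addresses multiplicity and does not remove the bias. The point concerns the supporting association analyses and the choice of parameters for the ROC curve. It is worth correcting, but it does not threaten the main comparison.

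**What to change.** - Under Structural parameters and Functional and perfusion parameters, specify partial Spearman correlation (on rank residuals) adjusted for age, education and BMI, computed within the migraine group, at the same corrected threshold.
- Under Correlation analysis, include the same covariates in the linear regression.
- Report the unadjusted coefficients alongside the adjusted ones.
- For hormone level, present both and do not treat the age-adjusted result as definitive.
- Define migraine history; if it means years since onset, say so.

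Cost: a few words in three sections and about three degrees of freedom from about 40. Age, education and BMI are already collected under Clinical assessments. Precision will fall somewhat where age and the clinical variable are collinear, as years of migraine may be. That loss reflects how little the data can separate the two.

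### The voxel-based structural maps are read in both directions at FWE P < 0.05 without saying that the 0.05 covers both; applied per direction, the error is about 10% per map

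*Protocol article*

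**What the plan says.** All places are in the protocol article.

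- **Subject** (sample size): "A sample size of 40 patients per group will be suitable for a power of 0.8 and an alpha significance level of 0.05 (two-side"). No effect size is given.
- **Statistical analysis** (opening paragraph): every test is at the 5% level, with sidedness not mentioned, and "SPM8 and REST 1.8 will be used to analyze the imaging data".
- **Structural parameters**: GMV, MK, MD and FA are compared between groups by two-sample t tests, both voxel-based and ROI-based, adjusted for age, sex, education and BMI. The threshold sentence reads "Significance threshold, which is corrected for comparison using Family Wise Error (FWE) method, will be set at" P < 0.05. The next sentence is "For each design matrix, significant effects both in the negative and positive directions are considered".
- **Primary outcomes measure**: white matter integrity, with MD, MK and FA as the examples.
- **Functional and perfusion parameters**: the same kind of t tests for ReHo, ALFF/fALFF and CBF, also at FWE-corrected P < 0.05. The sentence on directions is not repeated there.

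Nowhere does the article halve the threshold, name an F contrast, or say that the 0.05 applies to each direction.

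**The concern.** In SPM a t-contrast tests one direction. Its FWE-corrected P value is the probability, under the null, that the largest statistic in the image exceeds the observed one in that direction only. To look for both increases and decreases, the analyst runs the contrast and its negative. If each is judged at FWE 0.05, the map has two chances of a false positive and its error nearly doubles.

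The wording of the structural section fits that practice. Considering both signs for each design matrix is the language of paired contrasts in a general linear model, and the only threshold given is 0.05. The primary measures are among those tested this way. The section on correlation analysis then takes the most sensitive parameters into an ROC analysis, so a false regional finding could be carried forward as a candidate marker. The issue arises within each single map and is separate from the number of measures tested.

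**Working it through.** **Inputs**

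- Planned level: 0.05, two-sided (Subject).
- Voxel-wise threshold: FWE-corrected P < 0.05, both directions examined (Structural parameters).
- Degrees of freedom: 40 per group gives 80 − 2 = 78. Age, education and BMI remove three more, leaving 75. Sex is constant because only women are enrolled.
- Assumption: the number of effectively independent elements in a map is not given, so 2,000 and 55,000 are used as a range.

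**Step 1. Can the stated 5% be reproduced?** Yes, if 0.05 covers both directions. At 0.025 per direction the sum bound is 0.025 + 0.025 = 0.05. If the two directions are treated as independent, the error is 1 − 0.975² = 0.0494. A single two-sided test at FWE 0.05 gives the same level.

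**Step 2. What if 0.05 applies to each direction?** The sum bound is 0.05 + 0.05 = 0.10. Treating the two directions as independent gives 1 − 0.95² = 0.0975. Neither matches 5%.

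**Step 3. Simulation of null t maps with 75 df**, thresholds set for a one-direction family-wise error of 5% or 2.5%:

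| Independent elements | Both directions, 0.05 each | Both directions, 0.025 each |
|---|---|---|
| 1 | 9.6% | 4.8% |
| 10 | 9.8% | 5.0% |
| 100 | 9.8% | 5.2% |
| 500 | 9.4% | 4.9% |

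A separate run of 400 spatially smooth null maps (40 v 40, 16×16×16) gave 9.75%. That is 39 maps, with a standard error of √(0.0975 × 0.9025 / 400) = 1.5 percentage points, so the exact match with Step 2 is chance. These runs show what a per-direction threshold does. They cannot show that the plan uses one.

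**Step 4. Price of correcting it.** Bonferroni-type t thresholds with 75 df, at 0.05/V and 0.025/V:

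| Elements (V) | 0.05 per direction | 0.025 per direction | Rise |
|---|---|---|---|
| 2,000 | 4.30 | 4.49 | 0.19 |
| 55,000 | 5.18 | 5.35 | 0.17 |

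**The case against.** The strongest reply is that the doubling rests on a premise the article does not contain. It gives one corrected threshold and says that both signs are of interest. Read with the two-sided alpha in the sample-size paragraph, this may simply declare a two-sided test at 5% overall, which Step 1 reproduces. The software does not settle the matter, since REST 1.8 is named beside SPM8 and the type of contrast is not stated. A condensed article may also leave contrast coding to a fuller document. Finally, the sample-size alpha is generic and is not stated as an image-wide level, so setting it against an FWE threshold does not prove a contradiction.

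Much of this stands. A reader might infer that the primary tests, or all the imaging group comparisons, definitely run at about 10%. The documents do not support that, for three reasons:

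- No sentence assigns 0.05 to each direction.
- The ROI-based t tests, including those of MK, MD and FA, need not be directional SPM contrasts, and nothing suggests that they are one-sided.
- The sentence on directions appears only for the structural measures. For ReHo, ALFF/fALFF and CBF no error is shown.

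What the reply does not remove is the gap itself. This article chose to fix both the threshold and the two-direction rule, and the combination does not determine the error rate. The two-sided 5% reading also needs a step that is nowhere stated: a halved threshold or an F contrast. An analyst who follows the text in SPM8 with its ordinary t-contrasts would most likely apply 0.05 to each.

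**Conclusion.** The point holds as a conditional one, for the voxel-based structural maps only: GMV and the primary MK, MD and FA. The plan leaves the two-sided family-wise error per map undetermined between 5% and 10%. If FWE 0.05 is applied to each directional SPM t-contrast, the natural reading with SPM8, the error is about 9.75% and at most 10%, against the two-sided 5% used for the sample size.

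This assumes that the maps are thresholded through paired t-contrasts, that the FWE procedure is accurate in each direction, and that the intended level is two-sided 5% per map. The 10% bound does not depend on how the two directions are correlated.

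Severity is moderate. The primary measures are exposed and the remedy is nearly free, but the inflation is bounded at a factor of two and depends on a reading that the text allows without stating.

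**What to change.** In Structural parameters, add one sentence that fixes the level over both directions. Either of these will do:

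- each directional voxel-wise contrast is judged at FWE P < 0.025; or
- each measure is tested with a single F contrast at FWE P < 0.05, and the sign of any significant effect is reported afterwards.

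State as well that the ROI-based t tests are two-sided at 0.05. For consistency, adopt the same rule for the voxel-based ReHo, ALFF/fALFF and CBF contrasts in Functional and perfusion parameters.

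The cost is that sentence and a t threshold higher by about 0.17 to 0.2, with slightly less power in each direction. The loss cannot be put as a figure from the article, because it gives no effect size. If the sponsor already intended 5% over both directions, the change only records that intention and costs nothing.
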